### Secondary outcomes

The following secondary outcomes will also be collected as part of the intervention:Line Walk test which is a test to measure balance.Static Balance will be measured using Wii Balance Board, which have proven to be a valid measure of balance [19]. This measure will be done using an application developed by Francesco Sgró and colleagues [19].Adherence to trainingMotivation for trainingAcceptability of IMT

Adherence to the training will be measured by registering the number of times the participants participate and how much they participate at each session. Semi-structured interviews will be done with the participant after the intervention to investigate motivation and acceptability of the IMT.

### Sample size/power analysis

The data from the pilot study (described in Lund and Jessen [11]) was used to do a power calculation. The results showed that for a power of 80 there is a need for 20 persons in each group. As the population of community-dwelling elderly is expected to exhibit a high variance in functional abilities (higher than the population of the pilot study) we have increased the number of participants to 30 in each group. This also allows for dropouts from the study, which we experienced before initializing the pilot study.

### Statistical methods

#### Primary outcome analysis

Data will be collected from pre- and post-tests. Data will be analyzed for statistically significant differences by first checking that there is a Gaussian distribution and the using paired *t*-test, otherwise using Wilcoxon signed-rank test. The Wilcoxon Signed-Rank Test is selected because the population of community-dwelling elderly is expected to exhibit a high variance in functional abilities. Therefore a normal distribution of the population’s test scores cannot be assumed. The Wilcoxon Signed-Rank Test is a statistical hypothesis test suitable under such circumstances.

“Intention to treat” analysis will be done. These two conditions (ie, all participants, as randomized) are widely recommended as the preferred analysis strategy.

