## Methods/Design

### Objectives

The research hypothesis is that playful training here in the form of the IMT, will make participant perform better on the follow-up tests (6-min Walk Test (6MWT), the 8-ft Timed Up & Go Test (TUG), and the Chair-Stand Test (CS) from the Senior Fitness Test [10], than participants not using the IMT. Further it is expected that the participant will perform better on balancing tests (static test on Wii Board and Line Walk test), have a high degree of adherence (participation in +90% of the training), express that IMT is motivating for the training and IMT have a high acceptability.

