### Trial design

This study will investigate the use of one form of exergames called IMT, and how this compares to usual care of elderly people 70+. The trial will consist of two groups, one for training with the IMT and one group for usual care that will receive the care provided to non-patients elderly, which at this moment is no additional treatment other than recommendations.

The study will be a single blinded, randomized controlled trial. The study will be funded by the patient@home project, and equipment by Entertainment Robotics. Concealed allocation and intention-to-treat analysis will be used. Measurements will be taken at baseline and after intervention. Upon acceptance the protocol will be registered in clinicaltrials.gov.

Potential participants will be interviewed either by the primary investigator or student assistants at Center for Playware, and assessed for inclusion and exclusion criteria. After interviews the primary investigator will enroll participants. After pre-testing, the participants will be randomized and allocated to either control or intervention group (ratio 1:1) by an individual who is not involved in any of the other parts of the study. The randomization sequence will be created using the online platform www.randomization.com. Allocation will be done after pre-testing, as we have earlier experienced that some potential participants dropped out of the study just before starting.

The pre- and post-test will be done by an external physiotherapist blinded to the participants group allocation. The blinding will be done by using participation numbers and pre- and post-data will be obtained on different data-sheets. Participants, supervisors and care givers will not be blinded.

The trial’s results will be reported using domains and categories described in the taxonomy developed by the Prevention of Falls Network Europe, to allow future synthesis of evidence, or study replication [13].

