### Primary outcome

The primary outcome measures using pre- and posttests of the TUG, 6MWT and CS. The tests 6MWT, TUG and CS are described in the Senior Fitness Tests Manual [10]. The Senior Fitness Test [10] score fitness standards (performance cut points) that are associated with older adults ability to function independently. More than 2000 older adults have been scored, and the cut points’ accuracy and consistency have been validated as clear predictors of physical independence. The test can classify each individual into one of four levels (above average, normal range, below average or low functioning) and can be used to assess the individual’s health risk level.

Three different tests from the Senior Fitness Test [10] are focusing on health risk prevention, such as mobility, agility, balancing and general fitness, and are well established for testing a variety of health parameters in community-dwelling elderly. These tests include the 6MWT, the 8-ft TUG and the CS.

Studies have shown that the 6MWT can be used as a fall risk indicator specifically for frail elderly [14]. Furthermore, the 6MWT not only measures aerobic fitness and mobility, but also incorporates components of leg strength, balance, reaction time and vision.

It has been shown that the TUG reflects a combination of sensory, motor and strength abilities [15] and can be used as a measurement of functional mobility [16]. It has also been shown that the TUG can be a tool for discriminating between future fallers and nonfallers [14]. It has been demonstrated that the 8-ft version of TUG have similar qualities for agility and dynamic balancing and that this test is a reliable test for predicting future fallers and nonfallers from among the community-dwelling elderly population [17]. The CS measures lower body strength and endurance and the CS has been shown that the CS is a reliable and valid indicator of lower body strength in generally active, community-dwelling older adults [18].

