#### Secondary outcome analysis

Data from the LW test will be calculated in the same way as the primary outcomes.

Adherence will be calculated for the average and standard deviation for the participant. This will be compared to a goal of minimum 90% adherence to training.

Motivation will be based on the average scores and standard deviation from the participant interviews (questionnaire on motivation) as will the acceptability.

There are no other analysis planned for the study.

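### Baseline TUG, 6MWT and CS enter the primary analysis only by within-arm pre-post differencing; a baseline-adjusted between-arm model would supply the missing contrast with better precision

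*Protocol article*

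**What the plan says.** The Primary outcome section reads: "The primary outcome measures using pre- and posttests of the TUG, 6MWT and CS". Under Trial design, "Measurements will be taken at baseline and after intervention", and allocation follows the pre-test. Each participant therefore has a true pre-randomisation score on every primary outcome.

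Under Primary outcome analysis, the method is: "Data will be analyzed for statistically significant differences by first checking that there is a Gaussian distribution and the using paired" t-tests, "otherwise using Wilcoxon signed-rank test". No covariate or model is named. Under Secondary outcome analysis, the Line Walk test follows the same rule ("Data from the LW test will be calculated in the same way as the primary outcomes") and the list is then closed: "There are no other analysis planned for the study".

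The Objectives section states a between-arm hypothesis: tile users should do better "than participants not using the IMT". The sample size section gives 20 per group for 80% power, raised to 30 per group to cover higher variance and dropout.

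**The concern.** There are two layers.

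- **The contrast.** A paired test on pre and post scores asks whether an arm changed. It does not ask whether the arms differ. The plan names no test or estimate that sets the tile group against the control group, although that is the stated hypothesis.
- **The use of baseline.** The obvious small repair is to compare pre-post changes between arms. That would still use baseline inefficiently, because subtraction assumes that each unit of baseline carries through fully to the post-test. A model that estimates the slope is more precise whenever ρ is below 1.

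At stake are a primary result that does not address the hypothesis and, after a minimal repair, some loss of power from data already collected. Precision matters here because the plan expects wide variation ("As the population of community-dwelling elderly is expected to exhibit a high variance in functional abilities") with only 30 per arm.

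**Working it through.** **Inputs from the Protocol article:** 80% power at 20 per group; 30 per group planned; 1:1 allocation; pre- and post-tests on all three outcomes.

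**Not given, so assumed:** two-sided alpha 0.05; equal pre and post SDs; ρ shown at 0.5, 0.7, 0.8 and 0.9.

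**1. The plan's own figure.** The 20 per group cannot be reproduced without an effect size, SD and alpha. It can only be inverted. For a two-sample t-test, 80% power at 20 per group implies a standardised effect d = 0.909 (normal approximation: (1.960 + 0.842) × √(2/20) = 0.886). For a paired test it implies 0.660. The article does not say which was used.

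**2. What the named tests can show.** Suppose both arms truly improve by the same amount, 0.36 SD of the change, with 30 per arm. Each paired test is then significant for improvement with probability about 0.48. The pattern of significance in the tile arm alone arises with probability 0.48 × 0.52 ≈ 0.25, with no between-arm difference at all. A between-arm test would reject about 5% of the time. Simulation of 20,000 trials agrees.

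**3. Variance per participant of a between-arm contrast.**
- Change score: 2(1−ρ)SD²
- Baseline-adjusted: (1−ρ²)SD²
- Ratio: (1−ρ)(1+ρ) / [2(1−ρ)] = (1+ρ)/2

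**4. Power at 30 per arm** (noncentral t). The adjusted effect size is d × √(2/(1+ρ)); degrees of freedom are 58 for the change score and 57 for the adjusted model.
- *Case 1:* the stated 80% at 20 per group is taken as a between-arm change-score test, so d = 0.909.
- *Case 2:* higher variance has used up the increase to 30, so the change-score test has 80% power at 30 per arm and d = 0.736.

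| ρ | Variance ratio | Case 1: change score → adjusted | Case 2: change score → adjusted |
|---|---|---|---|
| 0.5 | 0.75 | 93% → 98% | 80% → 90% |
| 0.7 | 0.85 | 93% → 96% | 80% → 86% |
| 0.8 | 0.90 | 93% → 95% | 80% → 84% |
| 0.9 | 0.95 | 93% → 94% | 80% → 82% |

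**5. Chance imbalance.** The standard error of the baseline difference at 30 per arm is √(2/30) = 0.26 SD. Given an imbalance of that size, a change-score contrast is shifted by (1−ρ) × 0.26 SD: 0.13 SD at ρ = 0.5, 0.05 SD at 0.8 and 0.03 SD at 0.9. This is not a further loss on top of step 3. Since 2(1−ρ) = (1−ρ²) + (1−ρ)², the extra change-score variance is exactly the (1−ρ)² term that this residual produces.

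**The case against.** **The precision argument concerns an analysis the plan does not contain.** The plan names within-arm tests, so there is no between-arm change-score estimate to be inefficient. This stands. The missing between-arm comparison is the larger defect and the lack of a covariate is secondary. The covariate point keeps its own content, because a two-sample test of changes would cure the first and leave the second.

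**A reader might infer that chance baseline imbalance is left uncorrected, or that the estimate is biased.** The documents support neither. Subtraction does correct for baseline, with a slope of 1. It over-corrects and leaves (1−ρ) times the imbalance. Under randomisation the change-score contrast is unbiased, and the shift exists only conditionally on the imbalance observed and is already counted in its variance.

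**The size rests on unstated inputs.** This also stands. The rise from 80% to 90% needs both ρ = 0.5 and the assumption that higher variance exactly consumed the increase to 30. The pilot had no control group, so the 20 per group may come from a paired calculation. In that event the starting power is unknown: a two-sample effect of 0.66 would need 2 × (1.960 + 0.842)² / 0.66² ≈ 36.04, so 37 per arm.

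**Covariates are often left to an analysis plan.** This carries little weight here. The article names its primary tests and then says that no other analysis is planned, so the point concerns a stated method and not an omission.

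**Conclusion.** The concern holds in a limited form. As written, the primary analysis uses baseline only through within-arm differencing and gives no between-arm estimate for its hypothesis. If changes were instead compared between arms, estimating the baseline slope would cut the variance by 25% at ρ = 0.5, but by only 10% at 0.8 and 5% at 0.9.

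At 30 per arm the power gain is about 1 to 5 percentage points if the stated power is taken literally as a between-arm change-score figure. It is about 2 to 10 points if higher variance has used up the increase to 30. Both ranges assume two-sided 0.05, equal pre and post SDs and ρ between 0.5 and 0.9.

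A reader might go on to conclude that the trial is underpowered for want of a covariate. The documents do not give the figures to show that. The covariate alone is an efficiency improvement; the edit is worth making mainly because it also supplies the missing between-arm contrast.

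**What to change.** In Primary outcome analysis, replace the paired t-test or signed-rank rule for each of TUG, 6MWT and CS with a linear model of the post-test score on randomised arm and that outcome's own baseline score. Analyse participants as randomised and report the adjusted between-arm difference with a 95% CI.

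Prespecify robust (HC3) standard errors and a rank-based ANCOVA as a fixed sensitivity analysis, so that the method does not depend on a normality check of the trial data. Apply the same model to the Line Walk test in Secondary outcome analysis.

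The change is to wording only, with no new data, visits or participants. It costs one degree of freedom and assumes a roughly linear relation between baseline and post-test score.

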The Senior Fitness Test [10] scores have shown to be highly correlated with loss of functional abilities, as such keeping older adults physical active is the goal of this study. Investigating the functional capabilities of participants can give insights to how the IMT can help elderly avoid fall related injuries. Further, research has shown that barriers for elderly being physically active include poor health, fear of injury or lack of motivation, opportunities or companionship. Exergames have the potential to diminish some of these barriers.

There has been performed little research of this kind in the area of exergames as a tool to perform such exercises [2, 8].

A review and meta-analyse of exergames for older adults area found eighteen studies [8], an earlier review done at the point of planning this intervention found seven studies [2]. The reviews conclude that exergames have an overall positive effect on improving balance and mobility, but they also point to that there is a need for more studies with a higher degree of methodological quality (less risk of bias) [2, 8].

The goal of this project is to investigate and validate the use of one type of exergaming training tool the MOTO tiles to prevent loss of function abilities and decrease chance of falls among elderly people. The project will compare training with the MOTO tiles to usual care in the field with the aim of investigating whether the training will result in an improved physical abilities compared to usual care.

A pilot study of the use of the MOTO tiles in a municipality with no control group was conducted in 2012. This initial pilot study showed that the use of playware [3] technology for training and play could provide statistically significant progress in physical abilities [11]. The pilot study had 16 participants and significant improvement in the balance (Line walk – LW) (65%), endurance (6 min walking test - 6MWT) (26%), strength in the lower body (chair stand - CS) (20%) and dynamic balance and agility (Timed Up and Go - TUG) (18%) after just ten training times of 12–15 min per session [11]. In addition to the physical benefits, it was highlighted in subsequent interviews that it was fun to work out on the tiles, and 80% wanted to continue with this kind of playful training [7].

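### The only named tests compare before with after in the same people, so no planned analysis compares the two randomised arms

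*Protocol article*

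**What the plan says.** **Question.** The Background section of the protocol article sets up the trial "with the aim of investigating whether the training will result in an improved physical abilities compared to usual care". Objectives states the hypothesis for the 6-minute walk, Timed Up & Go and chair-stand tests as better performance "than participants not using the IMT".

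**Design.** Under Trial design, participants are "allocated to either control or intervention group (ratio 1:1"), after the pre-test. No matching of individuals across arms is described.

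**Data.** Under Primary outcome: "The primary outcome measures using pre- and posttests of the TUG, 6MWT and CS".

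**Analysis.** Primary outcome analysis makes the t-test for paired data the first choice: "Data will be analyzed for statistically significant differences by first checking that there is a Gaussian distribution and the using paired". If the Gaussian check fails, the fallback is also a test for paired data: "otherwise using Wilcoxon signed-rank test". The Methods paragraph of the Abstract says the same. Intention to treat is stated as the analysis principle.

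**Closure.** Secondary outcome analysis treats the Line Walk test like the primary outcomes. It summarises adherence, motivation and acceptability by mean and standard deviation, and ends: "There are no other analysis planned for the study".

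**The concern.** The question is about a difference between two independent groups. The tests named answer a different question: whether scores changed from pre-test to post-test in the same people. A significant paired test in the tile arm says that arm improved. It does not say that it improved more than usual care.

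Anything that moves both arms alike would therefore be credited to the training. Familiarity with the tests at the second sitting and a seasonal shift over 12 weeks are the obvious candidates. The Background says the 2012 pilot had no control group, and the trial was planned to supply the controlled evidence. If the analysis is followed literally, its p-values are of the same before-after kind as an uncontrolled study can give, and no effect estimate with a confidence interval emerges.

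**Working it through.** **1. Can the named tests be between-arm tests?** A paired t-test or a signed-rank test needs a pairing. The arms are individually randomised and unmatched, so the only pairing in the data is a person's own pre- and post-test. The test statistic is t = mean(D) / (SD(D)/√n), where D is post minus pre. The other arm's data do not enter it. Pooling the arms does not help, because that tests the overall change and ignores allocation. The reason given for the signed-rank test is possible non-normality, so the fallback leads to another paired test and not to a two-sample rank test.

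**2. Is a comparison of arms stated elsewhere?** No. Line Walk follows the same rule, the remaining secondary analyses are descriptive, and the list is explicitly closed. Intention to treat fixes who is analysed and in which arm. It adds no comparison.

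**3. Size of the consequence (illustration).** The article gives no expected change in controls, so a range is assumed. Inputs: 30 per arm (Sample size/power analysis); two-sided alpha 0.05 (assumed); no treatment effect; the same mean change m in both arms, in SDs of the change score (assumed).

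Probability p that the tile arm shows a significant gain: noncentral t with 29 df, critical value 2.045, noncentrality m√30.
- m = 0.2: noncentrality 1.095, p = 0.18
- m = 0.3: noncentrality 1.643, p = 0.36
- m = 0.4: noncentrality 2.191, p = 0.56

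Probability of the informal reading *significant in tiles, not in control*: p(1 − p), the arms being independent.
- m = 0.2: 0.15
- m = 0.3: 0.23
- m = 0.4: 0.25

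Simulation (40,000 trials per setting) gives the same values. In the same simulated trials a two-sample t-test on the changes rejects in 4.8% to 5.2% of trials for every shared change tried (0 to 0.8 SD).

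At least one of the three primary outcomes significant in the tile arm, with correlation 0.5 between outcomes (assumed, simulated): about 37%, 61% and 81%. Part of this is multiplicity, since with no shared gain the figure is already about 12.5%.

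**4. What the correct test means for the sample size.** The article reports 20 per group for 80% power but gives no effect size, SD, alpha or type of test, so that figure cannot be reproduced. It can be inverted at two-sided 0.05.
- If a two-sample test was powered: d = (1.960 + 0.842)·√(2/20) = 0.89, or 0.91 by the t distribution.
- If a paired test was powered: dz = (1.960 + 0.842)/√20 = 0.63, or 0.66 by the t distribution.

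In the paired case, a between-arm difference of 0.63 to 0.66 SD of change needs about 41 to 37 per arm for 80% power. With 30 per arm and no dropout, the two-sample t-test has about 66% to 71% power. The difference detectable with 80% power at 30 per arm is 0.74 SD of change.

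**The case against.** The best defence is that the analysis section never says the tests are run within each group. It speaks of differences with everyone analysed as randomised, and the rest of the article is framed as a comparison, so the authors may have meant to compare changes between arms and misnamed the test. Nothing confines the paired test to the tile arm either, and the data collected would support a valid comparison. This may be what was intended. But comparing changes between arms needs a two-sample t-test, a Mann-Whitney test or a regression on arm. None is named, and the article excludes further analyses. For the same reason this is not a detail left to a fuller document: the article states a test, and it is the wrong one.

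Some limits do stand:
- The percentages rest on assumed shared gains, and the any-of-three figures also on the correlation. With correlations from 0.2 to 0.8 they span about 30–43%, 51–68% and 72–88%. If all three outcomes had to succeed, at correlation 0.5, they would be about 4%, 13% and 30%. The article states neither success rule, nor the rule of significance in one arm only.
- Attention is not a shared influence, because controls do not train while the tile arm has group sessions. No between-arm test removes it. Regression to the mean has little support, since entry requires no performance threshold.
- ANCOVA is one valid choice among several.

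**Conclusion.** Wrong as written, and it must be corrected before analysis. The hypothesis is between arms, the only tests named are within person, and the plan excludes anything else. This follows from the text alone and needs no assumed figures. The illustration shows that the consequence can be large. With no treatment effect and a shared gain of 0.2 to 0.4 SD of change, a before-after success in the tile arm occurs in about 18% to 56% of trials per outcome, against about 5% for a test between arms. The simulated figures assume normal changes, 30 completers per arm and two-sided 0.05.

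**What to change.** In the Abstract and under Statistical methods, replace the paired tests with one between-arm analysis per outcome. ANCOVA is recommended: post-test score on randomised arm with the pre-test score as covariate, reporting the adjusted mean difference, 95% confidence interval and p-value. Care centre may be added as a covariate, since the Discussion mentions two centres. If a rank-based fallback is wanted, name a two-sample one, such as the Mann-Whitney test on change. Keep within-arm changes as description only. Use the same model for Line Walk and static balance, and amend the sentence that closes the list of analyses.

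The cost is rewording and a recheck of the sample size. No new data are needed, because the pre-test is taken before allocation. The sample-size section should say which test gave 20 per group and restate the calculation for the between-arm test. If a paired test was used, 30 per arm falls short of 80% power for the same effect. ANCOVA recovers some of that: relative to comparing change scores its variance is σ²(1 − r²) against 2σ²(1 − r), a ratio of (1 + r)/2. With an assumed pre-post correlation of r = 0.7 that is 0.85.

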**Methods:**

The study will be a single blinded, randomized controlled trial with 60 community-dwelling adults 70+ years. The trial will consist an intervention group of 30 participants training with the interactive modular tiles, and a control group of 30 participants that will receive the usual care provided to non-patient elderly. The intervention period will be 12 weeks. The intervention group will perform group training (4–5 individuals for 1 h training session with each participant receiving 13 min training) on the interactive tiles twice a week. Follow-up tests include 6-min Walk Test (6MWT), the 8-ft Timed Up & Go Test (TUG), and the Chair-Stand Test (CS) from the Senior Fitness Test, along with balancing tests (static test on Wii Board and Line Walk test). Secondary outcomes related to adherence, motivation and acceptability will be investigated through semi-structured interviews. Data will be collected from pre- and post-tests. Data will be analyzed for statistically significant differences by checking that there is a Gaussian distribution and then using paired *t*-test, otherwise using Wilcoxon signed-rank test. “Intention to treat” analysis will be done.

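### A normality check on the trial data picks the primary test, and signed-rank is justified by high variance: the reason is wrong, and the data decide which hypothesis is tested

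*Protocol article*

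**What the plan says.** In the protocol article, the Primary outcome analysis section sets a conditional rule. The analyst starts by "first checking that there is a Gaussian distribution"; if the check is passed a paired t-test is used, "otherwise using Wilcoxon signed-rank test". The Abstract (Methods) gives the same rule: "Data will be analyzed for statistically significant differences by checking that there is a Gaussian distribution and then using paired" t-tests, with signed-rank as the alternative.

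The reason for the alternative is then given: "The Wilcoxon Signed-Rank Test is selected because the population of community-dwelling elderly is expected to exhibit a high variance in functional abilities". From this the article infers: "Therefore a normal distribution of the population’s test scores cannot be assumed".

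The Primary outcome section lists three measures (TUG, 6MWT and CS), and the rule applies to each. The Secondary outcome analysis section treats the Line Walk test in the same way and says that nothing further is planned. The Objectives section states the hypothesis as a comparison: people who train on the tiles should do better at follow-up than people who do not.

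**The concern.** Three things in the reasoning do not hold.

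- A large variance does not make a distribution non-normal.
- The article speaks of the distribution of test scores, but both named tests depend on the pre-post differences.
- Signed-rank is presented as suitable when normality fails. It is a test of location only if the differences are symmetric, so it does not protect against the commonest departure, skewness.

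The rule also leaves the target of the primary analysis open until the data are seen. The paired t-test addresses mean change. Signed-rank addresses symmetry about zero, or the pseudo-median. TUG, 6MWT and CS could each be reported against a different target. Finally, whichever way the check falls, the chosen test compares pre with post within an arm and so does not answer the between-arm hypothesis.

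**Working it through.** **Inputs.** The sample size section gives the numbers per arm: "for a power of 80 there is a need for 20 persons in each group", and "we have increased the number of participants to 30 in each group". The rule is as described above, for three primary outcomes. The article gives no alpha or sidedness, no normality test, and no SD or shape for the differences. I assume two-sided 0.05, Shapiro-Wilk at 0.05 applied to the differences, and a range of shapes.

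**The plan's own figure.** The 20 per group cannot be reproduced from the article, because the effect size and SD behind it are not shown. Solved backwards at 80% power, it implies d = (1.960 + 0.842) × √(2/20) = 0.89 for two groups, or dz = (1.960 + 0.842)/√20 = 0.63 for a paired test. Nothing below depends on this; only n = 20 and n = 30 are carried forward.

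**Step 1: variance is not shape.** Let D = post − pre. The t statistic is mean(D)/(s_D/√n). Multiply every D by the same positive constant: numerator and denominator scale together, so t is unchanged. The signs of D and the ranks of |D| are unchanged, so signed-rank is unchanged. Shapiro-Wilk is also scale-free. Spread alone therefore cannot move any stage of the rule. Simulation agrees (20,000 null trials, n = 30, normal D): with SD 1 the check rejects in 0.050 of trials and the rule in 0.050; with SD 10 the figures are 0.051 and 0.053. The Monte Carlo standard error is √(0.05 × 0.95/20,000) = 0.0015. Moreover, stable differences in ability between people enter both pre and post and cancel from D.

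**Step 2: does the check inflate the error rate?** Rejection rates at n = 30, true mean change zero (20,000 trials each; gamma 4,000):

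| Shape of D | Check rejects | t fixed | Signed-rank fixed | Rule |
|---|---|---|---|---|
| Normal | 0.050 | 0.048 | 0.049 | 0.050 |
| t, 3 df | 0.454 | 0.045 | 0.051 | 0.051 |
| Uniform | 0.381 | 0.050 | 0.050 | 0.050 |
| Normal mixture, SD 1 and 3 | 0.510 | 0.047 | 0.050 | 0.051 |
| Gamma, shape 4 | 0.442 | 0.055 | 0.073 | 0.073 |
| Lognormal, sigma 0.5 | 0.719 | 0.067 | 0.117 | 0.115 |
| Exponential | 0.969 | 0.072 | 0.158 | 0.159 |
| Lognormal, sigma 1 | 0.992 | 0.117 | 0.331 | 0.331 |

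For symmetric shapes the rule stays between 0.047 and 0.053 across n = 20 and n = 30. For skewed shapes the rule column matches the signed-rank column, so the excess belongs to signed-rank and not to the act of choosing. A separate run of 4,000 trials gave the same picture: lognormal (sigma 0.5) 0.112 for the rule against 0.065 for t; exponential 0.165 against 0.074.

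**Step 3: how often would the three outcomes be split between tests?** If the check rejects with probability q for each outcome, and the outcomes are treated as independent for illustration, the chance that they do not all get the same test is 1 − (1 − q)³ − q³.

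- Normal, q = 0.05: 1 − 0.857 − 0.000 = 0.14.
- t with 3 df, q = 0.454: 1 − 0.163 − 0.094 = 0.74.
- Lognormal (sigma 0.5), q = 0.719: 1 − 0.022 − 0.372 = 0.61.

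The real outcomes are probably correlated, which would change these figures, but a split is not a remote possibility.

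**Step 4: within-arm against between-arm.** Suppose both arms improve equally by 0.3 SD of change (retest learning, for instance), so the tiles have no effect. With 30 per arm, a paired t-test in the training arm is significant in 0.359 of trials; a between-arm t-test is significant in 0.049. Choosing between the two paired tests in advance would leave this untouched.

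**The case against.** The strongest reply has four parts.

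- *The check does no measurable harm to the error rate.* This stands. A reader might infer that choosing a test from the data inflates type I error here; Step 2 shows that it does not. Even someone who took the smaller of the two p-values would reach only 0.055 to 0.063 with symmetric differences.
- *The rates for skewed differences are not errors of signed-rank.* This stands in part. Signed-rank tests symmetry about zero, and that null is false in those scenarios. If pre and post were exchangeable, the differences would be symmetric and the test would hold its level. The rates are errors only for a claim about mean change, and the article never says which claim it intends. The shapes are also assumed: the article gives nothing on the distribution of change, and mild skewness (gamma) gives only 0.073.
- *The passage is a conditional rule, not a contradiction.* This also stands. A reader might infer from the statement that signed-rank has been selected that two primary tests are named. The sentence can be read as explaining the fallback, and the Abstract gives only the conditional rule.
- *The name and cut-off of the normality test may sit in a fuller document.* Agreed; their absence is not part of this point.

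The reply does not rescue the stated rationale, which is wrong as printed. Nor can the between-arm comparison be presumed to lie elsewhere, because the article names only paired tests for these outcomes and says that no other analysis is planned.

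**Conclusion.** The rationale for signed-rank is wrong on three counts: variance is taken for shape, scores for differences, and signed-rank for a remedy against skewness. The first two follow from the definitions of the tests and need no assumption about the data.

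The practical effect of the check is on what is tested, not on the size of the test. With symmetric differences the rule keeps about 5%. With skewed differences it behaves like signed-rank and rejects a true zero mean change in about 11–16% of trials (lognormal with sigma 0.5, exponential), against about 7% for the t-test. The full range over the skewed shapes tried is 7% to 33%. These figures rest on two-sided 0.05, Shapiro-Wilk at 0.05, n = 30 and assumed shapes; they should not be read as the expected error rate of this trial.

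The within-arm form of both tests is the graver weakness of the same paragraph, and it makes settling for either test insufficient.

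**What to change.** In the Primary outcome analysis section and the Abstract, delete the normality check and the variance argument. Name one method in advance for TUG, 6MWT, CS and Line Walk: the post-test compared between the randomised arms with adjustment for the baseline value (ANCOVA). Use heteroscedasticity-robust standard errors, or a p-value from re-randomisation under the allocation scheme actually used, so that doubts about normality are met without a preliminary test. If a rank-based result is wanted, list it as a sensitivity analysis that compares the arms, such as rank ANCOVA or Wilcoxon rank-sum on change, rather than signed-rank.

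The cost is a rewritten primary analysis paragraph, a matching line in the Abstract, and slightly more analysis work. The pre- and post-tests already planned in both arms supply everything needed, so no new data are required.
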